### *Assessment of Causality*

The Investigator must assess the causality of each AE and SAE. Assessing causality involves consideration of whether there is a reasonable possibility that the event may have been caused by the treatment.

- **Not related:** AE for which there is evidence of another explanation, e.g. the AE is obviously explained by the participant's disease(s), is in accordance with the known effect of a concomitant medication or has occurred prior to first administration of study treatment.
- **Unlikely related:** AE with a time to study treatment administration that makes a relationship improbable (but not impossible), and disease or other drugs provide plausible explanations.
- **Possibly related:** AE with a reasonable time relationship to study treatment administration, but which could also be explained by disease or other drugs.
- **Probably related:** AE with reasonable time relationship to study treatment administration that is unlikely to be attributed to disease or other drugs.
- **Definitely related:** AE with plausible time relationship to study treatment administration, which cannot be reasonably explained by the known characteristics of the participant's clinical state, environmental factors, or other modes of therapy administered to the participant.

All AEs must be documented by the Investigator, regardless of causality.

### *Recording of Adverse Events*

All AEs that occur from the time of informed consent until the participant completes or withdraws from the study will be recorded in REDCap.

SAEs deemed possibly, probably or definitely related to study treatment occurring after the participant completes the study will also be reported to the Sponsor, or delegate, if the Investigator becomes aware of them.

It is preferable that AEs are reported as diagnoses if one is able to be made, rather than individual signs and symptoms. The AE description, onset and resolution dates, severity, causality and outcome must be recorded, as well as any actions taken.

Unless a diagnosis is made, or signs and symptoms are present, laboratory values or vital signs abnormalities should only be reported as AEs if they cause the participant to discontinue from the study, the Investigator feels it is clinically significant, or they meet a criterion for a SAE.

If an AE leads to premature discontinuation of the study, the appropriate pages of REDCap must be completed.

### *Reporting of Serious Adverse Events*

Investigators and other site personnel must report SAEs to the Sponsor or designee within 24 hours of becoming aware of the SAE, regardless of causality.

Follow-up information on SAEs must also be reported by the investigational site within the same time frame. If a non-serious AE becomes serious, this and other relevant follow-up information must also be provided within 24 hours.

All SAEs will be recorded in the participant records and REDCap.

#### *Follow-Up of Adverse Events and Serious Adverse Events*

All AEs and all SAEs must be followed by the Investigator until resolution, until the AE stabilises or is recognised as a permanent condition by the Investigator, or until the participant is lost to follow-up, whichever comes first. Follow-up investigations may be necessary according to the Investigator's medical judgement.

## **6 EFFICACY ASSESSMENT**

### **Ulcer Healing Assessments**

The Investigator/nurse will inspect the study ulcer at each site visit for physical (rate of healing) characteristics.

An ulcer will be considered completely healed if there is 100% reepithelialisation of the ulcer surface with no trace of exudate or drainage, as determined by the Investigator. The date of complete healing will be recorded as the date of the first assessment of 100% reepithelialization.

Note: if a participant withdraws from the study because their study wound is completely healed, they should complete Week 24 assessments.

### **Ulcer Infection**

Ulcer swabs will be taken as per Levine technique before and after application of rinse (PAW or control) at Weeks 1, 3, and 6. Samples will be processed by [name] team at the Basil Hetzel Institute.

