**Risk/Benefit Assessment**

As a first-in-human trial, some unforeseen risks to participants are unavoidable; however, all existing preclinical data highlights minimal risk to human cells and wound healing. As a topical application, it is highly unlikely that any application of PAW can have systemic effects. No participant will have PAW applied until completion of an ongoing large-animal (pig) preclinical study demonstrates no ill effects.

As a novel agent applied to open wounds, it is possible that localised skin irritation may occur; the trial and care team will be aware of this as the most likely adverse reaction and tailor a care plan for cases where it eventuates in order to limit impact of irritation on the wound microenvironment and healing.

Preclinical mouse and pig models showed no signs of pain or discomfort on application of PAW, and our patients with DFU, who are predominantly neuropathic, have a decreased capacity to feel localised foot pain. If patients with incomplete loss of sensation do report any pain or discomfort from the rinse application, saline will immediately be applied to wash away PAW and the event reported as an adverse reaction.

As a Phase I study in patients without severe infection, benefits to participants are expected to be muted. We expect participants randomised to the experimental arm of this study to have reduced bacterial load and recurrent infection during study; preclinical data suggests that wound healing may also be improved for this group. Regardless, we expect participants in both groups to benefit from improved personalised care experienced by typical clinical trial participants.

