### **Overview of Study Visits**

Study procedures should be performed at relevant study visits in accordance with the schedule of procedures outlined in Table 1. The Principal Investigator or other study doctor will be present for study treatment at screening and at the week two visit at minimum to ensure patient safety and observe for AEs.

Participants will only be enrolled and randomised to study treatment if they meet all eligibility criteria, and none of the exclusion criteria.

Study visits will be arranged at Royal Adelaide Hospital and/or The Queen Elizabeth Hospital, aligning with patient clinical visit scheduling where possible to minimise inconvenience to participants. A window of plus or minus three days is permitted for Visits 1 to 6, and a window of plus or minus seven days is permitted for follow-up Visits 7-10. Study visits via home visit are permitted for Visits 3-10.

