#### Criteria for Postponing or Stopping Study Treatment

##### *Prior to the Application of Treatment*

The treatment should not be applied if, in the opinion of the Investigator, there is a risk that the participant will be unable to tolerate treatment for any reason.

Treatment applications should be deferred if probable ulcer infection is noted. If treatment is deferred the patient can re-enter the trial at the point at which they left once the problem settles and at the Investigator's discretion.

Under these circumstances, at the discretion of the Investigator, study treatment may be postponed and initiated at a later time, provided that:

- The problem that resulted in postponement of the study treatment resolves, and is not considered by the Investigator to be likely to recur; AND
- The relevant visit is still expected to be completed within the stipulated visit window.

Alternatively, the participant may be withdrawn from the study.

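### Ulcer swabs are tied to a rinse that is deferred when infection is suspected, so swab results under-represent infected wounds

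*Protocol*

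**What the plan says.** **Swabs.** Protocol section 6, Ulcer Infection, is the only provision for study swabs: "Ulcer swabs will be taken as per Levine technique before and after application of rinse (PAW or control) at Weeks 1, 3, and 6". It names the weeks but defines each swab by its position before or after an application. It schedules no swab at a deferred visit, at an infection event, or in follow-up from Week 8 to Week 18.

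**Deferral.** Protocol section 7, Prior to the Application of Treatment, says: "Treatment applications should be deferred if probable ulcer infection is noted". It then offers three routes:

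- Resumption without a stated time limit: "If treatment is deferred the patient can re-enter the trial at the point at which they left once the problem settles".
- Postponement, on condition that: "The relevant visit is still expected to be completed within the stipulated visit window". For treatment visits, section 4, Overview of Study Visits, sets that window: "A window of plus or minus three days is permitted for Visits 1 to 6".
- Withdrawal: "Alternatively, the participant may be withdrawn from the study".

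**Expectation.** The Risk/Benefit Assessment states: "We expect participants randomised to the experimental arm of this study to have reduced bacterial load and recurrent infection during study". Bacterial load does not appear among the outcome measures in section 2 or in the Efficacy Analyses list in section 9.

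**The concern.** If the rinse is not given, there is nothing for a swab to be before or after. Whether a swab exists at a given visit therefore depends on whether the wound looks infected, and infection is what the swab is meant to characterise. This is informative missingness created by the data-collection rule. An SAP can describe how missing values are handled, but it cannot recover a sample that was never taken.

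The direction depends on what PAW does. If it reduces infection, as the protocol expects, control loses more of its infected-wound samples and the arms look more alike than they are. If it increases infection, the PAW arm loses more of them and the swab data look more reassuring than they should. At Weeks 3 and 6 the swab taken before the rinse is also the only microbiological look at whether any effect lasts between applications.

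**Working it through.** The protocol gives no figure to reproduce, so the check is to trace the two rules together and then illustrate the scale.

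**Step 1. Probable infection is noted at a swab visit.**

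| Route in section 7 | What happens to the swab pair |
|---|---|
| Postponed within the window | Taken only after the problem resolves. With a window of ±3 days this is at most 3 days after the nominal day, or 6 days after a visit held at the early edge (3 + 3). If the wound has not settled by then, there is no pair. |
| Re-entry at the point left | Taken after the problem settles, with no time limit in that sentence. |
| Withdrawal | Final visit procedures are sought, but Ulcer Infection schedules no swab there. |

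On each route, followed as written, the infected state is not sampled. The first two routes also disagree about how late the visit may be.

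The Week 1 swab can be affected too. The exclusion criteria rule out only moderate-to-severe infection, so a mildly infected ulcer can be enrolled and then meet the deferral rule.

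**Step 2. How many swabs are exposed.** The plan is 10 participants per arm and 3 swab weeks: 20 × 3 = 60 pairs, or 120 swabs, with 30 pairs per arm. Let p be the chance of deferral for probable infection at one swab week. The protocol gives no value, so p is assumed, and weeks are treated as independent. Then:

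- Expected pairs missing or postponed = 60p
- Chance that a participant has at least one affected pair: q = 1 − (1 − p)³
- Chance that an arm of 10 has at least one such participant = 1 − (1 − q)¹⁰

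| p (assumed) | Pairs affected of 60 | q | Arm has at least one |
|---|---|---|---|
| 5% | 3 | 14% | 79% |
| 10% | 6 | 27% | 96% |
| 20% | 12 | 49% | >99% |
| 30% | 18 | 66% | about 100% |

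**Step 3. What could be hidden.** Take the post-baseline swab visits, 10 × 2 = 20 per arm. Let infected wounds carry D log10 more bacteria than uninfected ones, let the infected fractions be pC (control) and pP (PAW), and let k be any direct reduction by PAW that is the same in infected and uninfected wounds.

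- Control minus PAW with every visit sampled: k + (pC − pP) × D
- Control minus PAW when infected visits are missing, or replaced by settled wounds with the uninfected load: k
- Hidden part: (pC − pP) × D

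All inputs below are assumptions:

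| pC | pP | D (log10) | Infected visits of 20, control / PAW | Hidden part (log10) |
|---|---|---|---|---|
| 0.20 | 0.15 | 1 | 4 / 3 | 0.05 |
| 0.30 | 0.10 | 1 | 6 / 2 | 0.2 |
| 0.30 | 0.10 | 2 | 6 / 2 | 0.4 |
| 0.30 | 0.10 | 3 | 6 / 2 | 0.6 |

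Over pC of 20-30%, pP of 10-15% and D of 1 to 3, the hidden part runs from 0.05 to 0.6 log10. If PAW had the higher infection rate, the sign would reverse.

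**The case against.** **No listed outcome is lost.** This stands. A reader might infer that the secondary outcome on infection is compromised, but the documents do not support that. Wound characteristics assessments (section 4) records signs of infection at each visit regardless of the rinse, and section 9 analyses infection as part of ulcer quality on the Monash tool. Reduced bacterial load is an expectation in the risk/benefit text, not an endpoint.

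**No safety signal disappears.** This also stands. A reader might infer that harm from PAW would go unseen. Adverse events (section 5) and wound characteristics would still record worsening; only the swab would be absent.

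**Efficacy is descriptive, with no formal sample size.** True, so no test result is at risk. A descriptive summary that omits infected wounds still misdescribes the arms.

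**Silence is not prohibition.** Staff could take the first swab before deciding to defer, and nothing forbids it. But nothing asks for it either, so practice may vary between staff. In the text available the schedule of procedures stops after vital signs, so a swab row could not be checked; the wording in section 6 ties the swab to the rinse all the same.

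**The arms would look identical.** A reader might infer this from the arithmetic. It holds only if all of the PAW effect comes through infection and every infected visit loses its swab. The protocol's rationale is direct killing, and that part (k) would still be observed.

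**Not every infected participant is affected.** Correct. The loss applies to probable infection noted at a swab visit, or to a sequence shifted by an earlier deferral.

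**Conclusion.** The concern holds within limits. Followed as written, sections 6 and 7 yield no swab, or a swab of a settled wound, when probable infection is noted at a Week 1, 3 or 6 visit. Swab summaries by arm would under-represent infected wounds and could conceal a difference in either direction.

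The effect is confined to the swab results, which are the only measurement under Ulcer Infection. The clinical infection outcome and adverse event recording are intact.

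The size cannot be known from the documents, which give no infection rates and do not say that culture will be quantitative. The 0.05 to 0.6 log10 range rests on the assumed rates and excess load above, and on every infected visit losing its swab or having it replaced by one from a settled wound. It is an illustration, not an estimate. The change is worth making because with 10 per arm each lost sample counts and the remedy is small.

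**What to change.** In Protocol section 6, Ulcer Infection, separate the first swab from the rinse: *the first swab is taken at the scheduled Week 1, 3 and 6 visit whether or not the rinse is given; the post-rinse swab is taken only if the rinse is given.* Record with each swab whether the rinse was given or deferred. Summarise the first swab over all participants seen that week, and the before/after change only in those rinsed.

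Separately, in section 7, reconcile the open-ended re-entry sentence with the visit-window condition, so that it is clear to which scheduled week a delayed swab belongs. Which clinical rule should apply is for the investigators; the swab change leaves the deferral rule as it is.

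The swab change costs one sentence and one form field. The downside is a few unpaired samples and an occasional extra swab when a deferred participant re-enters.

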### **Ulcer Pain**

Ulcer pain will be assessed using an 11-point Numeric Rating Scale (NRS). Participants will be asked to verbally rate the pain intensity in their study ulcer over the previous 24 hours as an integer from 0 to 10 (0 = no pain, 10 = worst possible pain). The majority of patients likely to be included in the study have peripheral neuropathy and are unlikely to feel pain at site; pain scores will be recorded nonetheless.

### **Contact Dermatitis assessment**

As the most likely adverse reaction to study treatment, all participants will be specifically monitored for contact dermatitis at study site throughout each study visit.

### **Quality of Life questionnaire**

Participants will be asked to complete a questionnaire to assess health-related quality of life (The Cardiff Wound Impact Schedule), as below (Figure 2). Use for academic projects is provided without charge.

|                                                                                                                                                                                                                                                                                                                                                                                                                                                                                                                                                                                                                                                                                                                                                                                                                                                                                                                                                                                                                                                                                                                                                                                                                                                                                                                                                                                                                                                                                                               |                               |                               |                          |                          |                          |        |                 |                          |                          |                          |                          |                          |  |                               |        |           |            |        |                                  |                          |                          |                          |                          |                          |  |                   |          |          |       |                |                                  |                          |                          |                          |                          |                          |                                                                                                                                                                                                                                                                                                                                                                                                                                                                                                                                                                                                                                                                                                                                                                                                                                                                                                                                                                                         |  |                               |          |            |             |      |                 |                          |                          |                          |                          |                          |  |                               |          |            |             |      |                                  |                          |                          |                          |                          |                          |
|---------------------------------------------------------------------------------------------------------------------------------------------------------------------------------------------------------------------------------------------------------------------------------------------------------------------------------------------------------------------------------------------------------------------------------------------------------------------------------------------------------------------------------------------------------------------------------------------------------------------------------------------------------------------------------------------------------------------------------------------------------------------------------------------------------------------------------------------------------------------------------------------------------------------------------------------------------------------------------------------------------------------------------------------------------------------------------------------------------------------------------------------------------------------------------------------------------------------------------------------------------------------------------------------------------------------------------------------------------------------------------------------------------------------------------------------------------------------------------------------------------------|-------------------------------|-------------------------------|--------------------------|--------------------------|--------------------------|--------|-----------------|--------------------------|--------------------------|--------------------------|--------------------------|--------------------------|--|-------------------------------|--------|-----------|------------|--------|----------------------------------|--------------------------|--------------------------|--------------------------|--------------------------|--------------------------|--|-------------------|----------|----------|-------|----------------|----------------------------------|--------------------------|--------------------------|--------------------------|--------------------------|--------------------------|-----------------------------------------------------------------------------------------------------------------------------------------------------------------------------------------------------------------------------------------------------------------------------------------------------------------------------------------------------------------------------------------------------------------------------------------------------------------------------------------------------------------------------------------------------------------------------------------------------------------------------------------------------------------------------------------------------------------------------------------------------------------------------------------------------------------------------------------------------------------------------------------------------------------------------------------------------------------------------------------|--|-------------------------------|----------|------------|-------------|------|-----------------|--------------------------|--------------------------|--------------------------|--------------------------|--------------------------|--|-------------------------------|----------|------------|-------------|------|----------------------------------|--------------------------|--------------------------|--------------------------|--------------------------|--------------------------|
| 
Physical symptoms and daily living
 
Have you experienced any of the following during the past week?
 
 
 	Not at all/
Not applicable	Seldom	Sometimes	Frequently	Always	
 
 Disturbed sleep						
 
 
Social life
 
Have you experienced any of the following during the past week?
 
 
 	Not at all/
Not applicable	Seldom	Sometimes	Frequently	Always	
 
 Difficulty getting out and about						
 
 
Well-being
 
To what extent do you agree/disagree with the following statements?
 
 
 	Strongly disagree	Disagree	Not sure	Agree	Strongly agree	
 
 I feel anxious about my wound(s)						
 
 |                               | Not at all/
Not applicable | Seldom                   | Sometimes                | Frequently               | Always | Disturbed sleep |  |  |  |  |  |  | Not at all/
Not applicable | Seldom | Sometimes | Frequently | Always | Difficulty getting out and about |  |  |  |  |  |  | Strongly disagree | Disagree | Not sure | Agree | Strongly agree | I feel anxious about my wound(s) |  |  |  |  |  | 
Physical symptoms and daily living
 
How stressful has this experience been for you?
 
 
 	Not at all/
Not applicable	Slightly	Moderately	Quite a bit	Very	
 
 Disturbed sleep						
 
 
Social life
 
How stressful has this experience been for you?
 
 
 	Not at all/
Not applicable	Slightly	Moderately	Quite a bit	Very	
 
 Difficulty getting out and about						
 
 |  | Not at all/
Not applicable | Slightly | Moderately | Quite a bit | Very | Disturbed sleep |  |  |  |  |  |  | Not at all/
Not applicable | Slightly | Moderately | Quite a bit | Very | Difficulty getting out and about |  |  |  |  |  |
|                                                                                                                                                                                                                                                                                                                                                                                                                                                                                                                                                                                                                                                                                                                                                                                                                                                                                                                                                                                                                                                                                                                                                                                                                                                                                                                                                                                                                                                                                                               | Not at all/
Not applicable | Seldom                        | Sometimes                | Frequently               | Always                   |        |                 |                          |                          |                          |                          |                          |  |                               |        |           |            |        |                                  |                          |                          |                          |                          |                          |  |                   |          |          |       |                |                                  |                          |                          |                          |                          |                          |                                                                                                                                                                                                                                                                                                                                                                                                                                                                                                                                                                                                                                                                                                                                                                                                                                                                                                                                                                                         |  |                               |          |            |             |      |                 |                          |                          |                          |                          |                          |  |                               |          |            |             |      |                                  |                          |                          |                          |                          |                          |
| Disturbed sleep                                                                                                                                                                                                                                                                                                                                                                                                                                                                                                                                                                                                                                                                                                                                                                                                                                                                                                                                                                                                                                                                                                                                                                                                                                                                                                                                                                                                                                                                                               |       |       |  |  |  |        |                 |                          |                          |                          |                          |                          |  |                               |        |           |            |        |                                  |                          |                          |                          |                          |                          |  |                   |          |          |       |                |                                  |                          |                          |                          |                          |                          |                                                                                                                                                                                                                                                                                                                                                                                                                                                                                                                                                                                                                                                                                                                                                                                                                                                                                                                                                                                         |  |                               |          |            |             |      |                 |                          |                          |                          |                          |                          |  |                               |          |            |             |      |                                  |                          |                          |                          |                          |                          |
|                                                                                                                                                                                                                                                                                                                                                                                                                                                                                                                                                                                                                                                                                                                                                                                                                                                                                                                                                                                                                                                                                                                                                                                                                                                                                                                                                                                                                                                                                                               | Not at all/
Not applicable | Seldom                        | Sometimes                | Frequently               | Always                   |        |                 |                          |                          |                          |                          |                          |  |                               |        |           |            |        |                                  |                          |                          |                          |                          |                          |  |                   |          |          |       |                |                                  |                          |                          |                          |                          |                          |                                                                                                                                                                                                                                                                                                                                                                                                                                                                                                                                                                                                                                                                                                                                                                                                                                                                                                                                                                                         |  |                               |          |            |             |      |                 |                          |                          |                          |                          |                          |  |                               |          |            |             |      |                                  |                          |                          |                          |                          |                          |
